### Sample size {14}

The aim of the study is to show that SPT is not inferior to PAP therapy in terms of daytime sleepiness measured with the ESS. A difference of 1.35 between the two means is proposed as the non-inferiority threshold, i.e. the hypothesis pair:$$H_0:\mu_{SPT}-\mu_{CPAP}\geq1.35\;vs.\;H_1:\mu_{SPT}-\mu_{CPAP}<1.35$$should be tested with a one-sided test at significance level of 2.5%.

This means that under the alternative hypothesis, the ESS value measured under SPT may not be more than 1.35 points higher on average than the ESS value under PAP therapy. The choice of the value for the non-inferiority margin is justified as follows: The study by Crook et al. investigated the size of the clinically relevant difference for the ESS. Depending on the method used, the difference was between 1 and 4.21 [12]. In other non-inferiority studies, a difference of 1.5 or 2 points was often chosen as the non-inferiority threshold [13]. One meta-analysis showed a difference between PAP vs. no therapy of 2.4 points (95% CI, 1.9 to 2.8) [14]. However, a more recent meta-analysis showed that this difference depends, among other things, on the baseline ESS and AHI. For example, a difference of 1.34 (0.68 to 1.99) was found for a baseline ESS > 10 points and AHI 5 to < 15/h and 2.22 (2.13 to 2.30) for an AHI 15/h to < 30/h [15]. Therefore, the size of the non-inferiority margin of 1.35 provided in the documents of Federal Joint Committee seemed appropriate to ensure at least a difference compared to no therapy in the planned study population.

Hence, sample size calculation was done using a one-sided one-sample *t*-test at a significance level of 2.5% and to achieve a power of 80% to test the above hypotheses. It was assumed that the difference between SPT and PAP is 0.8 points. Sample size calculation for a δ of 0.55 points (1.35–0.8), assuming a standard deviation of 4, results in a required sample size of 418 patients in total, i.e. 209 per sequence. A drop-out rate of 5% is assumed according to the studies by Berry and Mok, i.e. revocation or completely missing data after baseline [6, 13]. Therefore, a total of 440 patients, i.e. 220 per sequence, will be recruited into the study. Further missing values do not affect the sample size, as they will be replaced according to the analysis strategy.

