### Methods in analysis to handle protocol non-adherence and any statistical methods to handle missing data {20c}

Due to the non-inferiority study, missing values for the primary endpoint resulting from treatment discontinuation and non-completion of the corresponding ESS questionnaire are replaced by the baseline value. In the case of missing values under both interventions, no imputation should be performed, as this is generally anti-conservative in non-inferiority studies. These are therefore omitted from the analysis, and the modified intention-to-treat population is analysed. In addition, sensitivity analyses with the most conservative possible replacement of the missing values under both conditions should be carried out.

The missing values are not replaced for the analysis of the secondary outcomes.

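### Replacing a missing phase-end ESS value does not make it cost-free for power, so the reason the sample size section gives for making no allowance for one-phase missingness is wrong

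*Protocol article*

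**What the plan says.** All of this is in the protocol article.

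- **Sample size {14}**: the "sample size calculation was done using a one-sided one-sample *t*-test at a significance level of 2.5"% and was required "to achieve a power of 80% to test the above hypotheses". The margin is 1.35 points, the assumed true difference 0.8, the distance between them 0.55 and the SD 4. The result is 418 patients.
- The same section inflates this by 5% to 440. It defines that 5% as "revocation or completely missing data after baseline".
- For every other missing value it states: "Further missing values do not affect the sample size, as they will be replaced according to the analysis strategy".
- **Section {20c}** gives the replacement: "missing values for the primary endpoint resulting from treatment discontinuation and non-completion of the corresponding ESS questionnaire are replaced by the baseline value". Patients with neither phase value are not imputed and are left out.
- **Section {20a}** (analysis for the primary and secondary endpoints) accepts a patient into the primary analysis with a single post-baseline ESS value.

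**The concern.** A one-sample test in a two-period cross-over works on one SPT-minus-PAP difference per patient, so 418 counts patients with both values. A patient with only one value has no such difference. Writing the baseline ESS into the gap gives a row with a number in it, but that number says nothing about the missing therapy. The row then holds baseline minus PAP, or SPT minus baseline, and in general neither has the mean of 0.8 on which the 418 rests.

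The document expects such patients: it allows discontinuation in either phase, makes the cross-over after a first-phase discontinuation optional ({11b}), and admits one-value patients to the analysis. With only 0.55 points between the assumed truth and the margin, small shifts in the mean difference matter. At stake is whether the stated 80% can be read as a property of 440 recruited patients. The commissioning body, which approves the final report, is given no indication that it depends on one-phase missingness.

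**Working it through.** **Inputs from Sample size {14}.** One-sided alpha 0.025, margin 1.35, assumed difference 0.8, delta = 1.35 − 0.8 = 0.55, SD 4, complete loss 5%. That SD 4 is the SD of the paired difference follows from the one-sample test; the text does not say so in words.

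**Step 1: reproduce the plan's figures.** Power of the one-sample t-test comes from the noncentral t distribution with n − 1 degrees of freedom and noncentrality 0.55·√n / 4.

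- n = 417: 79.99%
- n = 418: 80.09%

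So 418 is the minimum. 418 / 0.95 = 440, and 440 × 0.95 = 418.0, so the 5% is used up by complete loss.

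**Step 2: power from complete pairs.** Let m be the share of the 418 with exactly one phase value. The document gives no m, so these are assumptions. Pairs = 418 × (1 − m).

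| m | complete pairs | power |
|---|---|---|
| 0 | 418 | 80.1% |
| 5% | 397 | 78.0% |
| 10% | 376 | 75.8% |
| 20% | 334 | 70.7% |

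If nobody were lost completely and all 440 gave pairs, power would be 82.1%.

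**Step 3: power under baseline replacement.** Let s and p be the shares missing under SPT only and under PAP only, c the mean ESS improvement from baseline under PAP, and d the true SPT-minus-PAP difference. The mean of the analysed difference is

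μ = (1 − s − p)·d + s·c − p·(c − d).

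Its SD comes from the three-part mixture, with SD 4 assumed within each part. Power uses noncentrality (1.35 − μ)·√418 / SD at d = 0.8. The type I error is the rejection rate at d = 1.35 (normal approximation). For c I take 1.34 to 4. The figures 1.34 and 2.22 appear in {14} as PAP versus no therapy, which is not the same as change from baseline; 3 and 4 are assumptions.

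*5% under SPT only* (s = 0.05, p = 0):

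- c = 1.34: μ = 0.95 × 0.8 + 0.05 × 1.34 = 0.827, SD 4.00, power 76%
- c = 2.22: μ = 0.760 + 0.111 = 0.871, SD 4.01, power 68%
- c = 3: μ = 0.760 + 0.150 = 0.910, SD 4.03, power 61%
- c = 4: μ = 0.760 + 0.200 = 0.960, SD 4.06, power 50%

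*3% under SPT, 2% under PAP, c = 2.2*: μ = 0.760 + 0.066 − 0.02 × 1.4 = 0.798, SD 4.02, power 80.0%.

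*5% under each therapy*: c cancels from the mean, so μ = 0.9 × 0.8 + 0.05 × 0.8 = 0.760. SD is 4.01 to 4.16 and power 85% to 82%. At d = 1.35, μ = 0.9 × 1.35 + 0.05 × 1.35 = 1.2825, which lies below the margin, and the rejection rate is about 5%.

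*5% under PAP only*: μ = 0.760 − 0.05 × (c − 0.8), which runs from 0.733 (c = 1.34) to 0.600 (c = 4). Power is 88% to 96%, and the rejection rate at d = 1.35 is 5% to 17%.

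**The case against.** **The arithmetic is right.** 418 and 440 both reproduce, and the sentence speaks of sample size, not power. Under {20a} and {20c} a one-value patient does stay in the analysis, so the analysed count is unchanged. All of this stands. But the sentence sits inside the power calculation as the reason for adding no allowance, and an unchanged row count does not preserve the power.

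**A stronger reading is tempting:** that the 80% holds only if all 418 patients have both values, or that any one-phase missingness must change the power. The document does not support either. Under the planned replacement, nominal power can stay at 80.0% (3% SPT, 2% PAP) or rise above it. Fewer complete losses than 5% would also offset some lost pairs. A match at 80% is, however, a coincidence of offsetting shifts, and the rises come from an estimate moved in favour of SPT.

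**The large losses rest on chosen assumptions.** The 50% needs all missing values under SPT and a PAP improvement that appears nowhere in the document; at 1.34 points the figure is 76%. This stands, and the range has to be shown whole.

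**Complete-pair power is not the planned analysis,** which imputes and fits a mixed model with baseline covariates. This also stands. Those figures measure the information lost and are not a forecast for the planned test.

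**Follow-up will limit the problem.** Patients who discontinue stay on schedule ({11b}), are asked for the primary endpoint anyway, by telephone if needed, and are invited to the second therapy ({18b}). This lowers the missing rate, and rates of 10-20% have no basis in the document. It does not make replacement cost-free.

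**Conclusion.** The concern holds as a wrong justification in the current text, not as an error in 418 or 440. The pure information loss is modest: about 2 points of power at 5% one-phase missing and about 4 at 10%, given 5% complete loss. Under baseline replacement the direction depends on which therapy's values are missing. With 5% under SPT only, nominal power is 76% to 50% for an assumed PAP improvement of 1.34 to 4 points. With 5% under each therapy it is 82-85%, with type I error about 5% instead of 2.5%.

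These figures rest on assumed missing rates and PAP improvements, on an SD of 4 for observed and filled differences alike, and on a one-sample test standing in for the planned mixed model. Whether baseline is the right replacement value is a separate question. The sentence would be wrong under any single-value replacement.

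**What to change.** In Sample size {14}:

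1. Delete the sentence on further missing values.
2. State that the 80% refers to 418 patients with both phase-end ESS values.
3. Keep the 5% as the allowance for complete loss after baseline, as now defined.
4. Add a short table for assumed one-phase missing rates (for example 5%, 10% and 20%) in addition to that 5%, split by therapy, giving power and also the one-sided type I error under the planned replacement. Label the rates and the PAP improvement as assumptions.

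This changes text only and asks for no additional patients. The cost is a small calculation and a stated power that becomes slightly less favourable.

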### Recruitment {15}

Recruitment was planned from Q4/2024 to Q2/2026 in approximately 15 German sleep centres. Before the start of the study, the centres were asked for an estimate of the number of patients who could be recruited during the study period. The total given from all study centres was approximately double the required sample size. As this trial is a cross-over study, it offers patients the opportunity to test both therapies, which is considered an advantage for recruitment.

Despite this, recruitment progress in the study sites is regularly monitored, and if a study site is significantly behind target, attempts are made to improve recruitment in consultation with the site. If this is not successful, this site will be closed and a new one opened.

## Assignment of interventions: allocation

### Sequence generation {16a}

Randomisation sequence (1:1 assignment) was generated using a computer-generated algorithm with randomly selected block sizes stratified by study centre and baseline AHI (mild vs. moderate) using the statistical software R, version 4.1.0 and the R package blockrand.

### Concealment mechanism {16b}

Randomisation will be done by the study physician via the electronic data capture system (EDCS, AlcedisTRIAL, Alcedis GmbH) after informed consent has been obtained from the study physician and the baseline data have been documented in the EDCS.

### Implementation {16c}

Allocation sequence will be generated by an independent statistician, who is not involved in enrolment and treatment of study participants.

## Assignment of interventions: blinding

### Who will be blinded {17a}

The study is an open labelled trial, so neither the patients nor the study physicians in the study centres are blinded to the therapy. The primary endpoint is self-reported by the patient, so it cannot be collected in a blinded manner. In addition, the statistical analysis will be done blinded; the evaluating statistician does not know the meaning of the group codes.

### Procedure for unblinding if needed {17b}

Since this is an open-labelled trial, no unblinding is necessary.

## Data collection and management

### Plans for assessment and collection of outcomes {18a}

Data from assessments and procedures will be collected following Table 1. All trial data will be collected through an electronic data capture (EDC) system. Project staff at the study centres will be trained in completing the electronic case report forms (eCRF) during initiation by the clinical research associates.

Patient reported outcomes (ESS, PSQI, FOSQ-10, EQ-5D-5L) are collected by paper and pencil and transferred to the EDC system by the study staff. Adherence data from the devices, for example nights and time used, are extracted from the device-specific app by the study staff and are then entered into the EDC system. There is no automatic import for this type of data to the EDC system due to the different manufacturers.

To ensure data quality of the primary and key secondary endpoints, on-site monitoring will be performed.

### Plans to promote participant retention and complete follow-up {18b}

To improve therapy adherence and participants’ retention, regular contacts via telephone calls or emails are planned. If it becomes clear during one of the contacts that the patient has dropped out of treatment, they are asked to participate in the outcome assessment, in particular of the primary endpoint, anyway. If the patient no longer wishes to come to the study centre, the primary endpoint can be collected by telephone. If drop-out of treatment was during the first therapy phase, the patient will be invited to receive the second therapy as planned.

### Data management {19}

For data capturing and data management of this clinical trial, a web-based validated software (AlcedisTRIAL) will be employed (eCRF). The development and setup is done by applying Good Automated Manufacturing Practice (GAMP) standards, fulfilling the FDA 21 CFR Part 11 and EU EudraLex V4 Annex 11 regulations. A set of Standard Operating Procedures (SOP) and guidelines are used during the study lifecycle project for supporting all study phases from specification, development, study start, deployment, and change management and up to study termination. To ensure high data quality, range checks will be made for numeric data at the time of data entry, and a warning will be displayed if the value does not meet the criteria. For categorical data, dropdown lists, radio buttons, and checkboxes will be preferred for data entry. All relevant fields, including all outcome measures, are marked as required fields so that data entry cannot be marked as complete before these data are captured; this will ensure collection of all outcome measures. The specifications of the checks applied to the data (both electronic checks and manual checks) are defined in the Data Validation Plan (DVP) including validation listings used for manual review. The DVP includes all definitions of electronic checks and the defined manual checks, which will be performed directly in the EDC system or can be based on listings. The data, as well as the medical review, are based on the defined manual checks of the DVP and are performed at regular intervals. Details of data management are defined in the data management plan.

The data processed by the Alcedis EDC systems is stored in a relational database. Specification and implementation of the database structure is based on the requirements of the particular study. The creation of the database is divided into several steps, which are specification, creation, field type verification, and structural verification. Any change in the database structure or its data is tracked. The database itself and its corresponding data at rest can be optionally encrypted. Access to the database is restricted.

Alcedis EDC systems are protected by mechanisms such as intrusion prevention and detection systems. Production data is separated from test and development data. The data processing takes place in data centres in Hessen/Germany. Encrypted backups are made daily and weekly. The daily backups are mirrored to a second data centre to prevent data loss in case of a local incident. Weekly backups are stored in a fireproof vault until they are delivered to a dedicated tape data archive. Data in transit, as when using the EDC system, is always encrypted.

### Confidentiality {27}

Pseudonymised personal data of participants will be stored in the EDC system (AlcedisTRIAL) in accordance with the German Federal Data Protection Act (BDSG). Data Access Groups (DAGs) will be used in the EDC system to restrict study staff access to data from their centre only. User rights will be restricted to the minimum necessary for individuals to perform their assigned tasks. Pseudonymisation is achieved through the use of unique centre numbers combined with consecutive patient numbers.

Re-identification can only be carried out in the study centre using the keylist. After the end of the trial, these keylists are destroyed as early as possible in accordance with the regulations. After the destruction, data will be fully anonymised.

### Plans for collection, laboratory evaluation and storage of biological specimens for genetic or molecular analysis in this trial/future use {33}

Not applicable, since no biological specimens have been collected.

## Statistical methods

The statistical analyses are carried out using the statistical software R (www.r-project.org), version 4.1.0 or higher. The analyses are blinded through the use of non-meaningful group codes, e.g. the groups are referred to as ‘Group A’ and ‘Group B’. For descriptive statistics, continuous variables are summarised using the arithmetic mean and standard deviation; in the case of a skewed distribution, the median and interquartile range are used. Categorical variables are summarised using totals and percentages.

Unless otherwise stated, for all confirmatory and exploratory analyses the estimate is given with the corresponding two-sided 95% confidence interval and the two-sided p-value. Two-sided *p*-values less than or equal to 5% or one-sided *p*-values less than or equal to 2.5% are considered statistically significant. The details of the planned statistical analyses will be specified later in the statistical analysis plan (SAP).

### Statistical methods for primary and secondary outcomes {20a}

#### Analysis sets

Three different analysis sets will be defined:

The *full analysis set* (FAS, based on the intention-to-treat (ITT) strategy) consists of all randomised patients according to the group allocation who fulfil the inclusion criteria and none of the exclusion criteria.

The *per-protocol set* (PPS) contains all patients from the FAS without serious protocol violations. The following protocol violations are categorised as serious:Discontinuation or intolerance regarding one of the two interventionsUse of the respective therapy devices for less than an average of 4 h per night or on less than 50% of the nights analysed

This is not an exhaustive list. The full list of all serious protocol violations leading to exclusion from the PPS will be determined as part of the statistical analysis plan, taking into account the protocol violations that actually occurred during the conduct of the study. The final list of protocol violations will be finalised before closing the database and starting the statistical analysis.

The *Safety Analysis Set* contains all randomised patients.

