**Methods:**

This is a multicentre, non-inferiority, open-label randomised, cross-over clinical trial. Patients with mild to moderate POSA and daytime sleepiness (according to Epworth Sleepiness Scale (ESS) > 10 points) will be randomised with a 1:1 allocation ratio, stratified by centre and AHI, to start with either PAP therapy or SPT and treated for 12 weeks. After a wash-out period of two weeks, they will switch to the other therapy for 12 weeks. The primary outcome is daytime sleepiness measured by the ESS at the end of each treatment phase. Analysis will be done in the intention-to-treat population using a linear mixed-effects model containing the intervention, the phase, the interaction between therapy and phase (including the carry-over effect) and the baseline measurement of the ESS and AHI as fixed effect, and centre and patient as random effects. A one-sided test at significant level of 2.5% will be used to test the non-inferiority of SPT with a non-inferiority margin of 1.35. Based on a sample size calculation with a one-sided one-sample t-test at significant level of 2.5%, assuming a standard deviation of 4, a total of 418 patients should be included to reach 80% power when SPT is only slightly inferior to PAP therapy (difference 0.8 resulting in a delta of 0.55 (1.35-0.8)). Assuming a 5% drop-out rate, 220 patients per sequence should be included. Possible futility stopping is planned at an interim analysis after 300 patients.

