### Criteria for discontinuing or modifying allocated interventions {11b}

Patients can withdraw their informed consent at any time without explanation. If the patient withdraws consent, no further data will be collected. The data already collected until that point will be stored and used for study purposes, if the participant does not request the deletion of their data. Data that has already been collected and included in analyses at the time of the request for data deletion remains unaffected by the deletion.

In case of proven failure of the above inclusion and exclusion criteria at baseline, the study participant may no longer participate in the study. This also applies if one of the exclusion criteria occurs during the course of the trial.

Study participants have the option to discontinue the intervention at any time without explanation. If a participant wishes to discontinue intervention, this is noted in the eCRF by the study staff, and the participant is asked for the reasons. In addition, the intervention can be discontinued by the attending physician in the event of intolerance of the intervention confirmed by the attending physician. Participants who discontinue intervention can continue to take part in the study and are then documented according to the protocol. They remain within the specified time schedule, i.e., in the event of a discontinuation of intervention during the 1 st intervention phase, the T1 and T2 visits take place at the specified times and, if desired, a cross-over to the respective comparative intervention in the 2nd intervention phase.

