#### Analysis for the primary and secondary endpoints

The aim of the study is to compare the use of the two therapies in terms of a treatment strategy. The difference in the ESS should therefore be determined without taking into account possible treatment discontinuations or compliance problems. For this reason, the analysis is conducted in a modified intention-to-treat population, which consists of all FAS patients with at least one value of the primary endpoint after baseline.

The *primary endpoint* is analysed using a linear mixed model. The model should contain fixed effects for the intervention, the phase, the interaction between therapy and phase (including the carry-over effect) and the baseline measurement of the ESS as well as the baseline AHI. Both the centre effect and the patient effect are modelled as random effects. The one-sided *p*-value corresponding to the hypothesis specified above, the estimated difference in ESS between the two treatments, and the corresponding one-sided confidence interval are reported. The one-sided *p*-value is calculated from the *p*-value of the above model either as p/2 or as 1-p/2 depending on the sign of the estimator. Details of the model, imputation of missing values, and sensitivity analysis are provided in the SAP.

The *secondary* quantitative endpoints are analysed using analogous models, with the difference that the baseline value of the endpoint under consideration is included in the model as a fixed effect instead of the baseline ESS. Analogous to the analysis of the primary endpoint, the p-value, the estimated difference, and the associated 95% two-sided confidence interval are also specified here. The analysis of dichotomous secondary endpoints is performed using mixed logistic regression models with the fixed effects for therapy, phase, and phase times therapy interaction as well as random effects for centre and patient. The analysis of count data, e.g. AHI, is performed with mixed Poisson models or, if necessary due to overdispersion, with negative binomial models with the fixed effects for treatment, phase, and phase times treatment interaction as well as random effects for centre and patient.

The secondary endpoints are analysed using two-sided tests at a significance level of 5%; all analyses of the secondary endpoints are exploratory.

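### The analysis set labelled intention-to-treat excludes randomised patients on eligibility with no time point stated, and the withdrawal rule for newly arising exclusion criteria permits treatment- or outcome-dependent loss from the primary analysis, of unknown size and direction

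*Protocol article*

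**What the plan says.** All references are to the protocol article.

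- **Analysis sets {20a}.** The FAS is presented as resting on the intention-to-treat strategy, but it "consists of all randomised patients according to the group allocation who fulfil the inclusion criteria and none of the exclusion criteria". No time point for the eligibility check and no adjudication procedure is given.
- **Analysis for the primary and secondary endpoints {20a}.** The primary analysis uses a "modified intention-to-treat population, which consists of all FAS patients with at least one value of the primary endpoint after baseline". The stated aim is a treatment-strategy comparison: "The difference in the ESS should therefore be determined without taking into account possible treatment discontinuations or compliance problems".
- **Abstract, Methods.** "Analysis will be done in the intention-to-treat population", with no mention of a modification.
- **Criteria for discontinuing or modifying allocated interventions {11b}.** For patients found ineligible: "In case of proven failure of the above inclusion and exclusion criteria at baseline, the study participant may no longer participate in the study". The next sentence extends this to later events: "This also applies if one of the exclusion criteria occurs during the course of the trial". The same section says of those who stop a device: "Participants who discontinue intervention can continue to take part in the study".
- **Participant retention {18b}.** Patients who drop out of treatment are still asked for the primary endpoint, by telephone if necessary.
- **Missing data {20c}.** A primary endpoint value missing because of treatment discontinuation and an uncompleted questionnaire is replaced by the baseline value. Patients missing under both interventions are omitted from the primary analysis and addressed in conservative sensitivity analyses.

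**The concern.** Two rules act together. One filters the FAS on eligibility without a time point. The other takes patients out of the study when an exclusion criterion arises after randomisation.

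Several criteria in {10} can follow from treatment or from the outcome itself. A limitation on side-sleeping could emerge under SPT, and {22} expects transient effects from the position the device imposes. Claustrophobia could emerge under a PAP mask. Vigilance-enhancing medication could follow persisting sleepiness under either therapy.

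The trial is open-label {17a}, so whoever records such a criterion knows the therapy. Under {23}, the first monitoring visit comes after the first randomised patient has finished phase 1. Ineligibility at baseline may therefore also come to light once treatment and response are known.

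At stake is the confirmatory test against the 1.35-point margin. If patients leave for reasons tied to their response, the estimate is no longer the treatment-strategy difference that the plan says it wants.

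**Working it through.** **1. The plan's own figures.** Inputs from Sample size {14}: margin 1.35, assumed difference 0.8, so δ = 1.35 − 0.8 = 0.55; SD 4; one-sided α 0.025; power 80%.

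- One-sample t-test (noncentral t): n = 418, power 0.801. The normal approximation (4 × (1.960 + 0.842) / 0.55)² gives 416.
- Drop-out: 418 / 0.95 = 440.

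Both stated figures reproduce, and the analysis-set rule does not alter them.

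**2. Who is kept and who can be lost.**

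- *Stops a device or cannot tolerate it:* stays in the study {11b}, is asked for the ESS {18b}, has a missing ESS replaced by baseline {20c}, and is removed from the per-protocol set only {20a}. Kept in the primary analysis.
- *Removed for a new exclusion criterion before any post-baseline ESS:* has no value of the primary endpoint, so is outside the modified intention-to-treat set. The sensitivity analyses in {20c} reach this patient only if the FAS filter is read as applying at baseline.
- *Removed for a new exclusion criterion after the phase 1 ESS:* can stay in the modified set, but the phase 2 ESS is missing. The replacement rule in {20c} is worded for treatment discontinuation with an uncompleted questionnaire. Whether removal under {11b} counts is not stated.
- *Found ineligible at baseline after randomisation:* outside the FAS. Harmless if judged on facts fixed before randomisation and without knowledge of sequence or outcome, but no such condition is stated.

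**3. Possible size.** The documents give no rate of such removals, so the share removed (f) and the distance e of the removed patients' SPT − PAP difference from the overall mean are assumptions.

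- Shift in the remaining mean = f·e / (1 − f)
- SE = 4 / √(418(1 − f))
- Type I error at a true difference of 1.35 = Φ(±shift/SE − 1.96), with + if SPT failures are removed and − if PAP failures are removed
- Power at a true difference of 0.8 when PAP failures are removed = Φ((0.55 − shift)/SE − 1.96)

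Example, f = 5% and e = 4: shift = 0.05 × 4 / 0.95 = 0.211; N = 397; SE = 4/√397 = 0.201; type I error = Φ(1.05 − 1.96) = 0.181.

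| f | e | N | shift | Type I error, SPT failures removed | Type I error, PAP failures removed | Power at 0.8, PAP failures removed |
|---|---|---|---|---|---|---|
| 1% | 2 | 414 | 0.020 | 0.032 | 0.020 | 77% |
| 1% | 4 | 414 | 0.040 | 0.040 | 0.015 | 74% |
| 2% | 2 | 410 | 0.041 | 0.040 | 0.015 | 73% |
| 2% | 4 | 410 | 0.082 | 0.061 | 0.009 | 66% |
| 5% | 2 | 397 | 0.105 | 0.076 | 0.007 | 60% |
| 5% | 4 | 397 | 0.211 | 0.181 | 0.001 | 39% |

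If removal is unrelated to outcome there is no shift, and power is 80% (f = 1%) to 78% (f = 5%). The calculation takes removed patients as lost entirely and all on one side. A mixture of SPT and PAP failures would partly cancel.

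**The case against.** The strongest reply is that the plan protects the primary analysis well. Discontinuation, intolerance and low use lead to exclusion from the per-protocol set only, and replacing a missing ESS by baseline counts against the therapy that failed. This stands. A reader might infer that treatment failures in general leave the primary analysis, but {11b}, {18b}, {20a} and {20c} say otherwise. Only failures recorded as a new exclusion criterion are exposed.

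Second, {11b} governs participation, not analysis sets, and no sentence says that an acquired criterion removes a patient from the FAS. Applied at any time, the FAS definition would be unworkable: every treated patient has ongoing device therapy, and a patient whose ESS falls to 10 or below would no longer meet inclusion. Eligibility at baseline is the more plausible meaning. This also stands, but it does not close the gap, because removal under {11b} still stops follow-up and can still leave a patient with no post-baseline ESS.

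Third, exclusion on facts fixed before randomisation need not bias the comparison. That is correct, provided the judgement is blind, which the article does not require.

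Fourth, details may sit in the statistical analysis plan. The article defers the model details, imputation, sensitivity analyses and the list of per-protocol violations, but it fixes the FAS itself. The timing of the eligibility check may be settled in the analysis plan. The end of ESS collection under {11b} is a matter of conduct and cannot be repaired there.

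Finally, the rule in {11b} also covers events such as pregnancy or a new cardiac device, so it cannot simply be struck out. This is accepted. The request is to reconcile the passages, not to change a clinical rule.

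**Conclusion.** The point holds in a limited form. The FAS is not an intention-to-treat set, its eligibility check has no stated time, and together with {11b} it permits loss that may depend on treatment or outcome. This conflicts with the population named in the abstract and with the treatment-strategy aim in {20a}.

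A reader might infer a bias towards non-inferiority. The documents do not support a fixed direction. Losing SPT failures favours SPT; losing PAP failures, for example after new claustrophobia, works against it. In a cross-over, a patient who leaves the analysis is also lost from both treatments.

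On the assumed grid the one-sided type I error could lie anywhere from about 0.181 down to 0.001, and power at a true difference of 0.8 could fall to 39%. These are illustrations. The documents support no particular share or difference, and the criteria are screened at entry, so only new-onset cases count. At 1–5% of 418, that is about 4 to 21 patients. The ambiguity should be settled before the database is closed, because the remedy is cheap and the test is confirmatory.

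**What to change.** 1. **FAS.** Define it as all randomised patients by allocated sequence. If exclusions are kept, limit them to criteria fixed before randomisation and judged by someone blind to sequence and outcome. Use later violations for the per-protocol set only.
2. **Follow-up.** Reconcile {11b} with {18b}, {20a} and {20c}. Whatever is decided clinically about an intervention when a criterion is acquired, this should not by itself end ESS collection in patients who have not withdrawn consent.
3. **Missing values.** State in {20c} that the baseline replacement covers ESS values missing after such a removal.
4. **Labels.** Align the abstract with the population actually analysed.

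The cost is a few sentences in the protocol and analysis plan and some extra ESS follow-up, for which telephone collection is already allowed. The planned 418 evaluable and 440 recruited patients do not change.
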